## Abstract

**Background:**

Ankle sprains are some of the most frequent injuries of the musculoskeletal system. However, there is no substantive evidence supporting which treatment strategy is superior. Taping with Kinesiotape (KT) is a new method that is used as an alternative to the more established taping and bracing techniques used for the prophylaxis and treatment of ankle sprains. The aim of this study is to examine the efficacy of KT on ankle sprain by comparing acupuncture combined with KT (AcuKT) with acupuncture alone in patients with acute lateral ankle sprains.

**Methods/design:**

This study is a prospective, multi-center (DongShin University Gwangju Oriental Hospital, DongShin University Mokpo Oriental Hospital, and KyungHee Korean Medicine Hospital), outcome assessor-blinded, randomized controlled clinical trial with a 1:1 allocation ratio. Participants (*n* = 60) with a lateral ankle sprain occurring within 1 week of the study will be randomly assigned to either an acupuncture group (*n* = 10 at each center (total *n* = 30)) or an AcuKT group (*n* = 10 at each center (total *n* = 30)). The acupuncture group will receive acupuncture treatment at ST36, ST41, BL60, BL62, KI3, KI6, GB39, and GB40 once per day, 5 days per week (excluding Saturday and Sunday) for 1 week. The AcuKT group will receive acupuncture treatment at ST36, ST41, BL60, BL62, KI3, KI6, GB39, and GB40 and the ankle meridian tendino-musculature and a figure-of-eight shape form of KT treatment once per day, 5 days per week (excluding Saturday and Sunday) for 1 week. The primary outcome will be pain evaluation assessed according to a Visual Analogue Scale (VAS), while Foot and Ankle Outcome Score (FAOS), edema, European Quality of Life Five Dimension-Five Level Scale (EQ-5D-5 L) score, and number of recurrent ankle sprains will be considered as secondary outcome measures. VAS, FAOS, and edema measurements will be performed at baseline (before intervention), 5 days after the first intervention (i.e.*,* at the end of the intervention), and 4 weeks after the completion of intervention. EQ-5D-5 L measurements will be conducted at baseline, 5 days after the first intervention, 4 weeks after the completion of intervention, and 26 weeks after the completion of intervention. The number of recurrent ankle sprains will be determined at 4, 8, 12, and 26 weeks after the completion of the intervention.

**Discussion:**

This study will provide data regarding the efficacy of KT for the treatment of acute lateral ankle sprain. The results may lead to insights into the usefulness of KT in the treatment of acute lateral ankle sprain.

**Trial registration:**

cris.nih.go.kr, ID: KCT0002257. Registered on 27 February 2017, and approved by the Ministry of Food and Drug Safety (Medical Device Clinical Trial Plan Approval #737).

**Electronic supplementary material:**

The online version of this article (10.1186/s13063-018-2527-5) contains supplementary material, which is available to authorized users.

## Background

Lateral ankle sprains are some of the most common musculoskeletal injuries [1]. Reported incidence rates range from 2.2 sprained ankles per 1000 person-years in the United States [2] to 5.3–7.0 sprained ankles per 1000 person-years in Europe [3, 4]. Ankle sprains are more serious than commonly believed because, in addition to the immediate onset of pain, swelling, and loss of joint motion, it has been reported that in 15–73% of lateral ankle sprain cases, chronic ankle instability with recurrent sprains and residual sensations of giving way may occur [5, 6]. Ankle sprains also result in high costs to society, due to increased healthcare resource use and work absence [7]. Ankle sprains are usually graded on the basis of the severity of the injury. Grade I is characterized by mild stretching or partial tearing of the anterior talofibular and/or calcaneofibular ligaments, accompanied by mild tenderness and swelling, but with only slight or no functional loss. Grade II is characterized by incomplete tearing of ligaments with moderate pain, swelling, and functional loss. Grade III is characterized by complete tearing of ligaments resulting in severe swelling, pain, and loss of function and motion [8].

The three main modalities of treatment for ankle sprains are surgical treatment, conservative treatment involving immobilization with a plaster cast or splint, and functional conservative treatment with tape, a semi-rigid brace, or a lace-up brace [9]. In 2015, ankle sprain was the fourth most common reason for visits to traditional Korean medicine (TKM) clinics, and 1.1 million Korean ankle-sprain patients received TKM treatment [10]. In TKM, complementary and alternative therapies are believed to relieve pain, reduce swelling, and help the body restore damaged tissue in cases of ankle sprain [7].

Taping with Kinesiotape (KT) is used as an alternative to the more established taping and bracing techniques for the prophylaxis and treatment of ankle sprains [11]. KT uses the newest form of elastic tape developed in the 1970s by [name], and was designed to yield therapeutic benefits while providing support and stability to muscles and joints without restricting the body’s range of motion [12, 13]. The tape used for KT differs from the traditionally used white athletic tape. It has unidirectional elasticity and, before applying it to the skin, it can be stretched to 140% of its original length so that it applies a constant pulling (shear) force to the skin. Furthermore, the tape used for KT is air permeable and water resistant, and can be worn for several days without removal [14, 15]. KT may assist in ankle sprain management by reducing pain, altering muscle function, improving circulation, enhancing proprioception, and repositioning subluxed joints [16].

## Methods/design

### Objective

The objective of the proposed study is to examine the efficacy of KT for the reduction of pain in patients with ankle sprain, and compare the efficacy of acupuncture combined with KT treatment (AcuKT) with that of acupuncture alone in patients with acute lateral ankle sprains (ALASs).

### Hypothesis

The null hypothesis is that, in ALAS patients, AcuKT does not improve the Visual Analogue Scale (VAS) score-determined severity of pain significantly more than acupuncture alone.

### Study design

Standard Protocol Items: Recommendations for Interventional Trials (SPIRIT) advice and Consolidated Standards of Reporting Trials (CONSORT) 2010 guidelines are followed below, to describe the design of this study [17, 18] (see Additional file 1). The proposed study is a prospective, outcome-assessor-blinded, multi-center (DongShin University Gwangju Oriental Hospital, DongShin University Mokpo Oriental Hospital, and KyungHee Korean Medicine Hospital), randomized controlled clinical trial with a 1:1 allocation ratio. A total of 60 participants who meet the inclusion and exclusion criteria will be randomly allocated to either an acupuncture group (*n* = 10 at DongShin University Gwangju Oriental Hospital; *n* = 10 at DongShin University Mokpo Oriental Hospital; and *n* = 10 at KyungHee Korean Medicine Hospital) or an AcuKT group (*n* = 10 at DongShin University Gwangju Oriental Hospital; *n* = 10 at DongShin University Mokpo Oriental Hospital; and *n* = 10 at KyungHee Korean Medicine Hospital). The acupuncture group will receive acupuncture treatment once per day, 5 days per week (excluding Saturday and Sunday) for 1 week, and the AcuKT group will receive acupuncture treatment and the ankle meridian tendino-musculature and figure-of-eight shape form of KT treatment once per day, 5 days per week (excluding Saturday and Sunday) for 1 week. VAS assessments, Foot and Ankle Outcome Scores (FAOSs), and edema measurements will be conducted at baseline (before intervention), 5 days after the first intervention (i.e., at the end of intervention), and 4 weeks after the completion of intervention. European Quality of Life Five Dimension-Five Level Scale (EQ-5D-5 L) measurements will be conducted at baseline, 5 days after the first intervention, 4 weeks after the completion of intervention, and 26 weeks after the completion of intervention. The numbers of recurrent ankle sprains will be determined at 4, 8, 12, and 26 weeks after the completion of intervention.

The design of the proposed study is in accordance with the recommendations of the Declaration of Helsinki, and was approved by the Ministry of Food and Drug Safety (Medical Device Clinical Trial Plan approval number 737. The trial has been registered at cris.nih.go.kr (KCT0002257). The study design is summarized in Figs. 1 and 2.

**Fig. 1 Fig1:**
[figure not shown]
Treatment schedule and outcome measures

**Fig. 2 Fig2:**
[figure not shown]
Study design flow chart

### Participant recruitment

Participants will be recruited at three hospitals in the Republic of Korea, DongShin University Gwangju Oriental Hospital, DongShin University Mokpo Oriental Hospital, and KyungHee Korean Medicine Hospital. The study will be publicized via local newspapers, the Internet, and posters in communities and hospitals. Participants will be given an explanation of the study by the Clinical Research Coordinator (CRC), and will voluntarily sign a form consenting to participation. The CRC will continuously monitor the medical conditions of enrolled participants to maximize adherence to intervention protocols.

### Inclusion criteria

Patients aged above 19 years of age, who have sustained a grade I or II ALAS within 7 days, and who voluntarily sign the informed consent form will be considered for enrollment. Grade-I ankle sprain is defined as no loss of function, no ligamentous laxity (i.e., negative anterior drawer and talar-tilt tests), little or no hemorrhaging, no point tenderness, total ankle motion reduced by ≤ 5°, and swelling ≤ 0.5 cm. Patients with some loss of function, a positive anterior drawer test (anterior talofibular ligament involvement), a negative talar-tilt test (no calcaneofibular ligament involvement), hemorrhaging, point tenderness, decreased total ankle motion > 5° but < 10°, and swelling > 0.5 cm but < 2.0 are defined as grade II [19].

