#### Primary outcome

Given that the objective of this study is to investigate the efficacy of KT on pain reduction in patients with ALAS, the primary outcome assessed will be changes in pain as determined via VAS, which is commonly used in clinical trials and other studies to determine primary outcomes. The VAS that will be used in this study is a 10-cm-long straight line marked at each end with labels that anchor the scale [24]. Patients will be asked to place a mark on the line at a point representing the severity of their pain, where the anchors are “no pain” and “pain as bad as it could be.” Scores are recorded in millimeters, thus yielding a total score range of 0–100 mm. The VAS is often treated as an interval-level scale (with equality between intervals) and subjected to arithmetic operations (e.g., calculation of change scores) and parametric statistics [25].

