### Sample size calculation

The sample size calculation is based on the primary outcome measure, pain, as determined via the VAS. In accordance with a previous study [30], we have established the number of groups at 2, the effect size as 0.906, with a one-sided alpha level of 0.025, and a statistical power of 0.8. Based on these parameters, the required sample size calculated using G*Power is 42 (21 per group). Estimating a maximum dropout rate of 30%, we have determined that a total of 60 participants—30 in each group—will be required.

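### The trial tests pain reduction but requires no pain at entry, so participants with little pain may enrol and dilute the group difference

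*Protocol article*

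**What the plan says.** The Objective section sets out to "examine the efficacy of KT for the reduction of pain in patients with ankle sprain". The Hypothesis is worded in terms of VAS pain, and under Primary outcome "the primary outcome assessed will be changes in pain as determined via VAS". The VAS is a 10-cm line anchored at no pain, "thus yielding a total score range of 0–100 mm". It is taken at baseline, at the end of the 5-day treatment, and 4 weeks after treatment ends.

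Inclusion criteria ask for age above 19, consent, and patients "who have sustained a grade I or II ALAS within 7 days". On grade I they state: "Grade-I ankle sprain is defined as no loss of function, no ligamentous laxity". They continue with "little or no hemorrhaging, no point tenderness, total ankle motion reduced by" at most 5°, and swelling of at most 0.5 cm. The Exclusion criteria remove grade III sprains, fractures and various comorbidities. Neither list mentions a pain score. The Background describes grade I less mildly: "accompanied by mild tenderness and swelling, but with only slight or no functional loss".

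The Sample size calculation takes from a previous study "the effect size as 0.906, with a one-sided alpha level of 0.025, and a statistical power of 0.8". It arrives at 21 per group, and at 60 in total after allowing for 30% dropout. It gives no SD, no difference in millimetres and no expected baseline VAS.

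**The concern.** The objective, hypothesis, primary outcome and sample size all concern pain, while eligibility is set by the grade and age of the injury. The grade I definition in the Inclusion criteria is mild enough to be compatible with a low pain score, particularly late in the first week. Someone who enters near 0 mm has almost no room to improve in either arm, and natural recovery by day 5 and by 4 weeks moves both arms further toward the floor. Such participants shrink the mean difference between arms.

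At stake is how a null result would be read. With an unknown number of low-pain participants, the trial could not tell whether Kinesiotape fails to reduce pain or whether there was little pain to reduce. Eligibility is fixed in the protocol, and this article gives it down to degrees and centimetres, so the point concerns the criteria as stated and not a detail left to another document.

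**Working it through.** **1. Reproduce the plan's figure.** Inputs from Sample size calculation: d = 0.906, one-sided alpha 0.025, power 0.80, two equal groups. For a two-sample t test, power = P(T > t_crit), where T is noncentral t with 2n − 2 degrees of freedom and noncentrality d·√(n/2).

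- n = 20 per group: power 0.797, just short.
- n = 21 per group: noncentrality 0.906 × √10.5 = 2.94, critical value 2.02, power 0.817.
- Total 2 × 21 = 42, and 42 / 0.70 = 60.

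The stated 21, 42 and 60 are all reproduced. With no dropout (30 per arm), power at 0.906 is 0.932. The arithmetic of the sample size is not in question.

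**2. What 0.906 means in millimetres.** The protocol gives no SD, so this is an assumed range. The between-arm mean difference is 0.906 × SD:

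- SD 15 mm: 13.6 mm
- SD 20 mm: 18.1 mm
- SD 25 mm: 22.7 mm

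This is an average difference between arms, not a change that each participant must reach.

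**3. Illustrative dilution.** Let p be the share of participants who can show no difference between arms. The protocol gives no value for p. With the SD held fixed, the diluted effect is 0.906 × (1 − p).

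| Assumed p | Effect | Power, 21 per arm | Power, 30 per arm |
|---|---|---|---|
| 0 | 0.906 | 0.817 | 0.932 |
| 10% | 0.815 | 0.732 | 0.874 |
| 25% | 0.680 | 0.575 | 0.735 |
| 40% | 0.544 | 0.405 | 0.544 |

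The 21-per-arm column applies if the full 30% dropout occurs. At 30 per arm, power is 0.808 at p = 18% and 0.798 at p = 19%, so it stays above 0.80 up to about 18%.

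**4. Sensitivity to the variance assumption.** Two alternatives bracket the fixed-SD model at p = 25%.

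- If participants at the floor have little spread, and baseline adjustment removes the spread between them and the rest, the effect is about 0.906 × √(1 − p) = 0.906 × √0.75 = 0.785. Power is 0.70 at 21 per arm and 0.85 at 30 per arm.
- If the mixture instead adds variance in the treated arm, the effect is 0.680 / √(1 + 0.25 × 0.75 × 0.906² / 2) = 0.655. Power is 0.54 and 0.70.

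So at the same p, power at 21 per arm runs from 0.54 to 0.70, against 0.82 planned.

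**The case against.** A reader might infer that grade I participants under these criteria will score near zero and so cannot show the effect. The documents do not support that. Absence of point tenderness is a finding on palpation, not a pain score. The same definition allows some swelling and lost motion, and the Background describes sprains as painful at onset and grade I as mildly tender. People who volunteer for five weekday hospital treatments are also less likely to be free of pain. This stands: the criteria permit low-pain participants, but nothing shows how many will enrol.

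A second tempting reading is that anyone entering below about 14 to 23 mm contributes nothing. That confuses a between-arm mean difference with an individual change. Such a participant can still contribute a smaller difference.

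Third, 0.906 is an average over the patients of the previous study. If that study also took grade I and II sprains with no pain threshold, any floor effect is already in the figure, and multiplying by (1 − p) counts it twice. The protocol does not describe that study's entry pain, so this cannot be settled and must qualify every power figure above.

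Fourth, the population is deliberate. The Discussion targets grade I and II sprains because their acute management is poorly defined, and it presents the results as preliminary. That is a fair reason for a broad population, but it does not explain why people without appreciable pain should count toward a pain endpoint.

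A reader might also fault the VAS prompt for not specifying rest or loading. That is not part of this point. An article commonly leaves measurement instructions to the full protocol, and changing the primary question in an ongoing trial would make early and late measurements inconsistent.

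**Conclusion.** The point holds as a mismatch between the trial's question and its entry criteria. Nothing requires pain at baseline, the grade I definition is compatible with little pain, and the outcome has a floor. Low-pain participants may therefore enter and dilute the comparison toward null.

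The size is unknown. Under the fixed-SD illustration, a 10% share costs about 8 percentage points of power at 21 per arm (0.817 to 0.732) and about 6 at 30 per arm (0.932 to 0.874). A 25% share costs about 24 points (to 0.575) and 20 points (to 0.735). These figures rest on an assumed share, an all-or-none effect, an unchanged SD, and a source study without the same mix. Relaxing the last assumption makes the loss smaller, and changing the variance assumption can move it either way. The figures are scenarios, not a forecast of the trial's power, and they give no reason to call the stated sample size miscalculated. The change is worth making because the needed measurement is already taken.

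**What to change.** - Add a minimum baseline VAS to the Inclusion criteria, at a threshold the sponsor chooses and justifies. A value such as 30 mm is only an example and has no support in the protocol. Under Randomization, baseline measurements precede allocation, so no new visit or instrument is needed.
- Keep everyone already enrolled in the primary analysis, whatever their baseline VAS.
- State that the primary comparison adjusts for baseline VAS. The Statistical analyses section names a repeated-measures ANCOVA but specifies no covariate, and lists the pre-intervention value among the dependent variables.
- Pre-specify a supportive comparison in participants at or above the threshold. In a trial of 60 it will have limited power and should be labelled accordingly.
- In the Sample size calculation, state the baseline VAS expected here and that of the study supplying 0.906, so that a reader can judge whether the effect carries over.
- Reconcile the two grade I descriptions, in the Background and in the Inclusion criteria.

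**Cost.** Recruitment will be somewhat slower, and conclusions will be limited to painful grade I and II sprains. Participants enrolled before and after the change will have met different criteria. Under Quality assurance, any revision needs approval from the Ministry of Food and Drug Safety and the three hospital IRBs. Because the trial is ongoing, the gain from the entry criterion shrinks as enrolment proceeds. The baseline adjustment and the supportive comparison remain useful at any stage before the data are analysed.

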### Exclusion criteria

Subjects whose general condition is unsatisfactory or who are not fit for acupuncture or AcuKT therapies will be excluded, as will those with a fracture as confirmed by x-ray, or a grade-III ankle sprain. Patients with near total loss of function, positive anterior drawer and talar-tilt tests, hemorrhaging, extreme point tenderness, total ankle motion reduced by > 10°, or swelling > 2.0 cm are defined as grade III [19]. Patients with a history of fracture in the same ankle during the previous year, a wound or skin disease at the KT attachment site, a serious disease (e.g., cancer, kidney disease, liver disease, disease of central nervous system, dementia, blood clotting disturbance such as hemophilia, etc.), a motor or sensory disturbance due to a nervous system disorder in the leg with the sprain, and women who are pregnant or breastfeeding will also be excluded.

### Ethical considerations

The Institutional Review Boards (IRBs) of DongShin University Gwangju Oriental Hospital, DongShin University Mokpo Oriental Hospital, and KyungHee Korean Medicine Hospital have all approved the study. The purpose and potential risks of this clinical trial will be fully explained to the participants and their families. All participants will be asked to provide written informed consent before participating in the study.

### Randomization

After written informed consent and baseline measurements are obtained, SPSS version 22.0 (IBM Corporation, Armonk, NY, USA) will be used to assign a serial number to the 60 research volunteers and to randomly allocate 30 of them into each group. The serial number codes will be inserted into opaque envelopes that will be sealed and kept in a double-locked cabinet, and opened in the presence of the patient and a guardian.

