### Statistical analyses

Baseline characteristics will be described and compared. Continuous data will be presented as means and standard deviations, and compared using the independent *t* test or Wilcoxon’s rank-sum test, while categorical data will be presented as frequencies and percentages and compared using the chi-squared or Fisher’s exact tests. A repeated-measures analysis of covariance (ANCOVA) will be conducted for the VAS of pain and the secondary outcomes (FAOS, edema, and EQ-5D-5 L). Dependent variables will include values measured before intervention, at the completion of intervention, and 4 weeks after the completion of intervention. A *t* test will be conducted to detect differences between therapies, and repeated contrast tests will be conducted to account for time differences in each group. A *p* value of < 0.05 will be considered significant, and participants who drop out of the study will be excluded from the analysis (i.e.*,* a per-protocol analysis will be performed). All statistical analyses will be performed using SPSS version 22.0.

Data from participants who adhere to < 80% of the protocol procedures (i.e., receive fewer than four of the five scheduled treatments) will be excluded. Missing values will be implemented by multiple imputations. In addition, differences between subjects who complete the study and those who drop out will be analyzed statistically to investigate whether any particular factors are significantly associated with dropping out. Interim analyses will not be performed.

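### The design fixes 10 per arm at each of three centres, but the Randomization section describes one 30:30 split of 60 with no centre structure; read literally, it gives the stated allocation about 5% of the time

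*Protocol article*

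**What the plan says.** All references are to the protocol article.

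- **Study design:** "A total of 60 participants who meet the inclusion and exclusion criteria will be randomly allocated to either an acupuncture group" or an AcuKT group. The same sentence gives the count in each arm as "10 at DongShin University Gwangju Oriental Hospital", with the same number at each of the other two hospitals. All six cells are therefore fixed at 10. The Abstract gives the same counts, and the trial is called a "randomized controlled clinical trial with a 1:1 allocation ratio".
- **Randomization:** after consent and baseline measurements, SPSS is used "to assign a serial number to the 60 research volunteers and to randomly allocate 30 of them into each group". The codes go into sealed opaque envelopes. Centre, strata, blocks and separate lists are not mentioned.
- **Implementation:** one role, the clinical research coordinator (CRC), generates the sequence, enrols participants and assigns them.
- **Statistical analyses:** a repeated-measures ANCOVA "will be conducted for the VAS of pain and the secondary outcomes", and a t test compares the therapies. No covariate is named, for centre or anything else.

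**The concern.** A reader who follows the Randomization section would make one list of 60. A reader who follows Study design would make three lists of 20. These are different procedures, and only the second guarantees the per-centre counts that the article states as part of its design. This is more than a detail left to a fuller document, because the article describes a method and that method, as worded, does not produce the allocation described elsewhere in the same article.

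The answer also affects the analysis. If allocation is forced to 10:10 within centres, centre has been balanced by design. A comparison that ignores centre then leaves the between-centre variance in the error term and overstates the standard error of the treatment difference.

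**Working it through.** **Inputs.** 60 participants, 30 per arm (Randomization; Sample size calculation). Three centres with 10 per arm each, so 20 per centre (Abstract; Study design). Effect size 0.906, one-sided alpha 0.025, power 0.80, dropout 30% (Sample size calculation). The documents give no centre variance, so a range is assumed in step 4.

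**1. The plan's own figure.** For a two-sample t test (noncentral t), power is 0.797 at 20 per arm and 0.817 at 21, so 21 per arm and 42 in total. Allowing for dropout, 42 / (1 − 0.30) = 60. The stated sample size reproduces, and 60 / 3 = 20 per centre. Nothing here is in dispute.

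**2. Chance that one 30:30 split gives 10:10 everywhere, with exactly 20 per centre.**

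P = C(20,10)³ / C(60,30) = 184,756³ / (1.1826 × 10¹⁷) = 0.0533

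That is about 1 in 19, so the split misses the stated allocation 94.7% of the time. For a single centre:

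- P(10:10) = C(20,10) × C(40,20) / C(60,30) = 0.215.
- The SD of the AcuKT count is √(20 × ½ × ½ × 40/59) = 1.84.

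**3. How uneven it would be.** Enumerating all splits (a, b, 30 − a − b) over the three centres:

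| Worst centre | Probability |
|---|---|
| 12:8 or worse | 0.68 |
| 13:7 or worse | 0.35 |
| 14:6 or worse | 0.13 |

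If the centre totals were also left to chance, with each patient equally likely to come from any centre (an assumption), the chance of 20/20/20 is 0.0136. The chance of the full stated design is then 0.0136 × 0.0533 = 0.0007.

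**4. Ignoring centre after 10:10 allocation in each centre.** If centre accounts for a share ρ of the outcome variance, the unadjusted standard error is too large by a factor 1/√(1 − ρ), and the real two-sided alpha is 2 × [1 − Φ(1.96/√(1 − ρ))]:

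- ρ = 0.10: factor 1.054, alpha 3.9%.
- ρ = 0.20: factor 1.118, alpha 2.8%.

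Simulation with a fixed variance share of 10% and 20% gives 3.8% and 2.7–2.8%. With centre effects drawn at random at an intraclass correlation of 0.10 and 0.20, it gives 4.2–4.3% and 3.7–3.8%. Hence roughly 3–4% instead of 5%.

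**5. Direction of the error.** One-sided rejection rates under no effect (nominal 0.025; 8,000 simulated trials per case; intraclass correlation 0 to 0.20):

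- Allocation by centre, unadjusted: about 0.026 falling to 0.019.
- Allocation by centre, adjusted: 0.025 to 0.026.
- One split, unadjusted: 0.021 to 0.024.

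No case shows material inflation; 0.026 is within simulation error of 0.025.

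**6. Cost of two centre terms.** Power at 21 per arm goes from 0.817 to 0.816. At 30 per arm it is 0.932 either way.

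**The case against.** **The Randomization section never says that allocation is unstratified.** Three lists of 10:10 also total 30 per group, and Study design puts the per-centre counts inside its allocation sentence. Read together, the sections are compatible with allocation by centre. This stands as far as it goes: a single unstratified split is the literal reading, not an established fact, and the 5% applies only under that reading. The mismatch remains, because the stratified reading has to be brought in from another section.

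**Centre is absent from the analysis.** A reader might take this as a defect in its own right. The documents do not support that: Statistical analyses names no covariate at all, and model terms are commonly left to an analysis plan, which is not shown. Centre in the model is recommended here only because it follows from allocating by centre.

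**Bias or confounding with centre.** A reader might infer this from uneven centres. Chance imbalance under a valid random split is not bias, and step 5 shows that type I error is not inflated. Nor do the documents describe differences between hospitals in referral mix or assessors; the Intervention section says that practitioners are trained together in the same techniques.

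**Sixty acute patients cannot be assembled and then split.** The order of the sentence invites this reading, but the sealed envelopes make sequential use of a prepared list feasible.

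**The type I error figures rest on an assumed centre variance.** That is so. Moreover, the primary outcome is change in VAS, so stable centre differences cancel and only centre differences in change would matter. The true effect could be smaller than shown.

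**Small blocks are predictable in an open-label trial, and the CRC both generates the sequence and enrols.** This also stands, and it shapes the fix.

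**Conclusion.** Wrong as written on the allocation, with a free improvement in the analysis. The method in the Randomization section, read literally and with 20 patients per centre, gives the 10:10 counts in all three centres with probability 0.053, and leaves at least one centre at 12:8 or worse with probability 0.68. The sections must be reconciled.

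If allocation is by centre, as Study design implies, an unadjusted comparison is conservative by an amount that depends on the unknown centre variance. The consequences are an allocation that may not match the stated design and some lost precision. The sample size is unaffected.

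**What to change.** - **Randomization:** state that the sequence is generated before first enrolment as a separate 1:1 list for each centre, 20 per centre and 10 per arm. If blocks are used, keep their sizes hidden from whoever enrols.
- **Implementation:** reconcile this section with that change. Block sizes cannot be hidden from the enrolling CRC if the same person generates the list, so the two tasks need to be separated.
- **Statistical analyses:** include centre as a fixed factor in the primary and secondary efficacy models.
- **If allocation has already taken place:** the trial is described as ongoing, so report the method actually used and correct whichever section is inconsistent with it. If a single list was used, the fixed per-centre arm counts in the Abstract and Study design should go.

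The cost is three short lists instead of one, a second person to generate them, and two model degrees of freedom. With exactly 20 recruited per centre, separate 10:10 lists deliver the stated counts with certainty.
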